#### Randomisation

Prior to receiving their test result, probands with an ICC in whom a likely pathogenic or pathogenic variant is identified will be randomly assigned to either the intervention or control group. Block randomisation will be used, with variable blocks ranging from size two to six. Randomisation will be stratified for gender, disease type (cardiomyopathies or primary arrhythmia syndromes) and hospital. To ensure allocation concealment, computer software will be used for randomisation, with an allocation rate of 1:1.^32^ Relatives of probands included in the study will be assigned to the group to which the proband was assigned.

Neither participants nor genetic counsellors will or can be blinded for group assignment. The executing researcher also cannot be blinded because of slight differences between the questionnaires administered in the intervention and control groups. Part of the outcome data will be collected using telephone interviews. To minimise bias, these interviews will be conducted by a research assistant following a structured script.

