#### Measurement time points

For secondary outcome measures, participating probands will be asked to complete a questionnaire 1 month after receiving the genetic test result (T1) and to complete a second questionnaire 9 months after the test result (T2). Before T1 and T2, a short structured telephone interview will be conducted about participant’s knowledge of which relatives are at risk of ICCs and which relatives are informed, because these items are expected to be too complex to answer in a questionnaire.^33^ Participating relatives will complete one questionnaire after attending genetic counselling.

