### Participants’ characteristics

To assess whether randomisation succeeded and whether characteristics of participating probands and relatives have influenced the primary and secondary outcome measures, sociodemographic and clinical factors will be collected, including gender, education level, ethnicity, living situation and parenthood, family history and the diagnosis of the probands at T1. Relatives will additionally be asked what their degree of kinship is with the proband.

For the same reason, psychosocial and personality factors will be assessed in both probands (at T1) and relatives. Coping style will be assessed by using the shortened version of the Threatening Medical Situations Inventory (TMSI).^37 38^ The TMSI assesses a ‘monitoring’ versus ‘blunting’ coping style related to a medical threat, and it was previously evaluated in an oncogenetic patient population.^37 39^ The shortened version of the TMSI contains two subscales, both consisting of six items on a 5-point Likert scale (1 = ‘Totally not applicable’ to 5 = ‘Totally applicable’; range 6–30). Reliability and validity are satisfactory.^37 38^ The Trait subscale of the State Trait Anxiety Inventory (STAI) will be administered to assess trait anxiety in both probands and relatives.^40^ The STAI is frequently used in research settings and consists of 20 items on a 4-point Likert scale (1 = ‘Not at all’ to 4 = ‘Very much so’; range 20–80).^40^ The reliability and validity for the Dutch translation of the STAI are assessed as good.^41^

Self-efficacy and perceived motivators and barriers regarding informing relatives at risk will be assessed using an adapted version of the ‘motivation’ and ‘self-efficacy’ subscales of the Informing Relatives Inventory (IRI).^42^ The IRI was developed and evaluated in an oncogenetic patient population, and showed satisfactory reliability and validity.^42^ The ‘motivation’ subscale consists of 30 items on a 5-point Likert scale (1 = ‘No role’ to 5 = ‘A large role’; range 30–150), and the ‘self-efficacy’ subscale consists of 7 items on a 4-point Likert scale (1 = ‘Not sure at all’ to 4 = ‘Very sure’; range 7–21). Probands will also be asked to answer a self-constructed item during the telephone interviews regarding whether relatives were informed and whether probands intended to inform (remaining) at-risk relatives.

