### Data analysis

#### Statistical analysis

Sociodemographic, clinical, psychosocial and personality variables will be analysed using descriptive and frequency statistics. An intention-to-treat approach will be used. SPSS V24.0 will be used to perform statistical analyses.^44^ An α level of p<0.05 will be used. Analysis of variance and χ tests will be used to assess differences (1) in sociodemographic, clinical and psychological characteristics between the intervention and control groups and (2) in participants and non-participants, as appropriate. Descriptive and frequency statistics will be used to describe the primary outcomes: (1) uptake of genetic counselling and (2) uptake of predictive DNA testing. Logistic regression analysis will be conducted to assess differences between the intervention and control groups on the primary outcomes, with the randomisation group as the main exploratory variable. Two logistic regression models will be used, with the first model including only the randomisation group and the second model also including the potential covariates (ie, sociodemographic, clinical and psychological variables). Multilevel analyses will be performed to assess whether the randomisation group, that is, the independent variable, has an impact on family and psychological functioning, that is, the secondary outcome variables. The two measurement time points in probands will be treated as nested within probands. To prevent influence of potential confounding factors, multilevel analysis will be adjusted for covariates as well. Participant appreciation of the approach used will be described using frequency statistics.

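### The adjusted uptake model includes psychological variables measured after randomisation, and in relatives only after attendance, so its group effect can be biased or, on one reading, not estimable

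*Protocol article*

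**What the plan says.** Under Statistical analysis, two logistic models are planned for uptake of counselling and of predictive DNA testing: one "with the first model including only the randomisation group", and "the second model also including the potential covariates (ie, sociodemographic, clinical and psychological variables"). Covariates are not restricted to pre-randomisation values. The section does not say whether they are the proband's or the relative's, or which model carries the conclusion.

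The timing is set elsewhere in the protocol article:

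- Randomisation: "Prior to receiving their test result, probands with an ICC" and an identified variant are allocated, stratified by gender, disease type and hospital.
- Intervention group and Control group: the allocated approach is discussed at post-test counselling.
- Measurement time points: probands "complete a questionnaire 1 month after receiving the genetic test result (T1"). For relatives, "Participating relatives will complete one questionnaire after attending genetic counselling".
- Participants' characteristics: "psychosocial and personality factors will be assessed in both probands (at T1) and relatives". In addition, "Self-efficacy and perceived motivators and barriers regarding informing relatives at risk will be assessed", and risk perception is recorded. The stated purpose of this data collection begins "To assess whether randomisation succeeded and whether characteristics of participating probands and relatives have influenced" the primary and secondary outcomes.
- Primary outcome measures: the denominator is all eligible at-risk relatives in the pedigree, whether or not they attend.

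**The concern.** A covariate in the analysis of a randomised comparison should be one that allocation cannot have changed. Here the proband has already been through the post-test session before answering. In the intervention arm that session offered to let the counsellor inform some relatives. Confidence in informing relatives, reasons for and against informing them, and perceived risk to them could all differ by arm because of that session. Conditioning on them changes what the group coefficient measures. It no longer estimates the total effect of the approach, and it may also pick up unmeasured factors that drive both the score and uptake.

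Relatives' questionnaires raise a separate problem. They exist only for people who attended, so having the covariate implies a positive counselling outcome.

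The same T1 data are meant to show whether randomisation succeeded. A difference between arms in a score that the intervention can move does not answer that question.

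**Working it through.** **1. The plan's own figure.** Inputs from Sample size calculation: uptake 50% and 65%, two-sided 5%, power 80%. With pooled variance and mean proportion 0.575,

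n per group = [1.960·√(2·0.575·0.425) + 0.842·√(0.50·0.50 + 0.65·0.35)]² / 0.15² = 169.3, rounded up to 170.

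The total is 340, and 85 probands × 4 relatives = 340. The plan's figure is reproduced and is not in dispute.

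**2. Order of events.** Randomisation → test result and post-test counselling (allocated approach discussed) → T1 at one month. For relatives: being informed → attending counselling → questionnaire. No psychological covariate comes before allocation.

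**3. If relatives' own scores enter the second model.**

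- Expected attenders: 170 × 0.50 + 170 × 0.65 = 85 + 110.5 = 195.5.
- Expected non-attenders: 170 × 0.50 + 170 × 0.35 = 85 + 59.5 = 144.5, about 145 of 340. None has a questionnaire.
- Complete cases: at most 195.5, all with counselling uptake = 1. If 70% of attenders respond (an assumption, since the protocol gives 70% for probands only), 195.5 × 0.70 ≈ 137 remain, again all equal to 1.

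The counselling outcome is then constant and a logistic model cannot be fitted. For DNA testing, only attenders remain, so the model estimates testing given attendance. The protocol defines that separately as conditional uptake.

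**4. If proband T1 scores enter the second model.** The documents give no effect of allocation on these scores, so a range was assumed. A large-sample simulation used 100,000 probands with four relatives each:

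score = a·group + standard normal error; logit(uptake) = b₀ + t·group + g·score.

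The constants b₀ and t were set so that uptake is exactly 50% and 65%. The true total difference is therefore 15 points in every row (odds ratio about 1.86). The last column standardises the adjusted model over the score.

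| Shift in score (a, SD) | Log-odds per SD (g) | Adjusted odds ratio | Adjusted difference, points |
|---|---|---|---|
| 0 | 0.5 | 1.94 | 15.2 |
| +0.3 | 0.5 | 1.66 | 11.6 |
| +0.5 | 0.5 | 1.49 | 9.1 |
| +0.5 | 0.8 | 1.35 | 6.4 |
| -0.3 | 0.5 | 2.25 | 18.4 |

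In the first row the odds ratio rises slightly with no bias in the difference. This is the usual non-collapsibility of the odds ratio. Adding an unmeasured common cause of score and uptake (loading 0.7 on the score, log-odds 0.5 on uptake, g = 0.3) gave 11.7 points for a shift of 0.3 and 9.3 points for a shift of 0.5.

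**The case against.** The strongest reply is that the randomised comparison survives. The unadjusted model rests on laboratory and pedigree data, needs no questionnaire and is untouched. This stands. A reader might infer that the primary result as a whole is invalid, and the documents do not support that.

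Second, the article does not say whose covariates enter. With proband-level covariates the model can be estimated, and the Participants section says relatives complete the questionnaire to measure secondary outcomes. This also stands, so the failure to estimate is conditional. It is not a strained reading, however, because Participants' characteristics links the characteristics of both probands and relatives to the primary outcomes.

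Third, most listed covariates are unlikely to be moved by allocation. Of 18 that can be counted, only six (motivation, self-efficacy and four risk-perception ratings) are plausibly affected. The other 12 are demographic, clinical or trait-like. Since the covariates are called potential, 18 is an upper count. This narrows the point to those six and to relatives' data.

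Fourth, the article admits, among its limitations, that intention to inform and psychological functioning at baseline cannot be controlled for. That admission does not cure the model. It confirms that later scores cannot stand in for baseline values.

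A reader might also take 20% drop-out off the 85 families and conclude that 17 families, about 68 relatives, leave the adjusted model. The documents do not support this. The 759 to be approached comes from 85 / 0.20 / 0.70 / 0.80 = 758.9, so the 85 is already net of drop-out. The article states neither a T1 non-response rate nor complete-case deletion.

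**Conclusion.** The concern holds for the second, adjusted uptake model. Its covariate set, as written, takes in variables measured after the allocated approach was discussed or only in relatives who attended.

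- **Proband scores.** The size is unknown. Over the assumed range, a true 15-point effect is reported as anything from 6.4 to 18.4 points. The bias is nil if allocation does not move the scores. A reader might infer that adjustment must shrink the effect, but the direction depends on how the scores respond, which the documents do not tell us.
- **Relatives' scores.** If they are entered, the result follows from the design. About 145 of 340 relatives lack them at the planned uptake, the counselling model has no outcome variation, and the testing model targets a different quantity.
- **Randomisation check.** A T1 difference in self-efficacy, motivation or risk perception is not evidence that randomisation failed. The check remains reasonable for stable characteristics.

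The point matters because the article does not say which model is the main one, so the affected estimate could be presented as the definitive adjusted result. The sample size is not affected.

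**What to change.** 1. Name the model with randomisation group plus the stratification factors (gender, disease type, hospital) as the primary inference for both uptake outcomes.
2. Limit any further adjusted uptake model to variables fixed before randomisation and known for all eligible relatives: the stratification factors and pedigree data such as the relative's sex, age and degree of kinship.
3. Use stable proband characteristics such as education and parenthood only if they can be taken from a source available for all probands. The article collects them at T1. Only the three stratification factors are shown to be known at randomisation.
4. Move T1 self-efficacy, motivation and risk perception, and all relatives' questionnaire data, to uptake analyses labelled exploratory.
5. Drop those three T1 measures from the check on randomisation.
6. Do not adjust the secondary multilevel models for them.

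The cost is mainly rewording, with no change in sample size. The adjusted model has fewer covariates. Finding a complete source for proband education or parenthood would take some extra work if those variables are wanted.

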**Methods:**

A multicentre randomised controlled trial with parallel-group design will be conducted in which an intervention group receiving the tailored approach will be compared with a control group receiving usual care. Adult probands diagnosed with an ICC in whom a likely pathogenic or pathogenic variant is identified will be randomly assigned to the intervention or control group (total sample: n=85 probands). Primary outcomes are uptake of genetic counselling and predictive DNA testing by relatives (total sample: n=340 relatives). Secondary outcomes are appreciation of the approach used and impact on familial and psychological functioning, which will be assessed using questionnaires. Relatives who attend genetic counselling will be asked to fill out a questionnaire as well.

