### Objectives

The primary aim of this randomised controlled trial is to assess whether uptake of genetic counselling and testing of relatives at risk of an ICC will be increased by using a tailored approach to information provision for relatives, instead of usual care (ie, the family-mediated approach). Secondary objectives are to evaluate how such a tailored approach is appreciated by both probands and relatives as compared with usual care. In addition, this study aims to assess the perceived impact on family relationships and psychological functioning of both probands and relatives. The protocol presented here has been described based on the ’Standard Protocol Items: Recommendations for Interventional Trials (SPIRIT) statement.^31^

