#### Secondary outcome measures

Secondary outcome measures will be measured using both validated and self-constructed questionnaire items. An overview of these items is shown in the online supplementary material S2. Secondary outcome measures include the following:
*Appreciation of the information provision strategy used and preferences regarding the approach used to inform relatives at risk*: This will be evaluated in both probands and relatives using self-constructed items on a 5-point Likert scale (1 = ‘Totally disagree’ to 5 = ‘Totally agree’) in a questionnaire (probands: five items, range 5–25; relatives: six items, range 6–30). Probands will be asked to answer an additional self-constructed item during the structured telephone interview about whether they would have preferred to inform their relatives differently. Two additional self-constructed items will be administered in the intervention group to assess decisional conflict in probands, including whether probands thought it was difficult to choose to inform their relatives themselves or have them informed by the counsellor, and whether they were satisfied by their decision, on a 5-point Likert scale (1 = ‘Totally disagree’ to 5 = ‘Totally agree’; range 2–10). Probands will be asked to fill out these items at T1. At T2, a self-constructed item will be administered to assess whether their opinion regarding the approach used has changed. The questionnaire for relatives also includes a self-constructed item on how they were informed (ie, by whom they were informed and what information was provided). Finally, probands (at T1 and T2) and relatives will be asked whether they visited the website www.erfelijkehartziekten.nl and, if yes, how they evaluated the website, using four self-constructed items on a 5-point Likert scale (1 = ‘Totally disagree’ to 5 = ‘Totally agree’; range 4–20).

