### Sample size calculation

The study aims to detect a difference of 15% in uptake of genetic counselling by relatives between the control (usual care, 50%) and intervention groups (tailored approach, 65%). Assuming a two-sided 5% significance level and a power of 80%, 340 relatives (170 in each group) would be required to participate in this study. On average, six relatives per proband are at 50% risk of inheriting the variant, including children and adults.^9^ With a conservative estimate of four eligible adult relatives per proband at risk, 85 probands with an ICC and an identified likely pathogenic or pathogenic (class 4 or 5) variant will need to be included in this study to reach 340 relatives. A likely pathogenic or pathogenic variant is found in, on average, 20% (lower margin) of all probands with a suspected ICC. With an expected response rate of 70% and a drop-out rate of 20%, approximately 759 probands will be approached to participate in the study.

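### Appreciation is set as a comparison with usual care, but only frequency statistics are planned for it, so no between-arm estimate or interval is pre-stated

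*Protocol article*

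**What the plan says.** The Objectives section of the protocol article states the aim comparatively: "Secondary objectives are to evaluate how such a tailored approach is appreciated by both probands and relatives as compared with usual care". The strengths and limitations list repeats the contrast, setting acceptance under the tailored approach against acceptance under the standard one, in probands and relatives. The abstract names appreciation first among the secondary outcomes: "Secondary outcomes are appreciation of the approach used and impact on familial and psychological functioning".

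Secondary outcome measures describes summed Likert scores ("probands: five items, range 5–25; relatives: six items, range 6–30"), with the proband items completed at T1. Only one set of items is restricted to one arm: "Two additional self-constructed items will be administered in the intervention group to assess decisional conflict in probands".

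Statistical analysis assigns methods as follows:
- **Primary outcomes:** descriptive and frequency statistics to describe them, then logistic regression to assess the difference between groups.
- **Family and psychological functioning:** multilevel models with randomisation group as the independent variable.
- **Appreciation:** "Participant appreciation of the approach used will be described using frequency statistics".

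**The concern.** The objective asks for a contrast between randomised groups, and the method named for it is descriptive. The multilevel sentence does not close the gap. It asks whether randomisation group "has an impact on family and psychological functioning, that is, the secondary outcome variables", which leaves appreciation out of a list in which the abstract and the measures section include it.

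The Introduction gives possible pressure, worry, loss of autonomy and strain on family relationships under active approaches as the reason for tailoring. The section on patient involvement says burden was not assessed beforehand because it belongs to the outcome measures. How the approach is received relative to usual care is therefore part of the trial's rationale. Without a pre-stated estimate and interval, readers will judge a difference between two columns of frequencies by eye. They may read chance as preference, or dismiss a real difference.

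**Working it through.** **1. Does any sentence of the plan yield a between-arm result for appreciation?** The methods in the article's data analysis part, taken in turn:

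| Method | Applied to | Covers appreciation? |
|---|---|---|
| Analysis of variance and χ tests | Sociodemographic, clinical and psychological characteristics, by arm and for participants against non-participants | No |
| Logistic regression on randomisation group | The two uptake outcomes | No |
| Multilevel model on randomisation group | Family and psychological functioning | No |
| Frequency statistics | Appreciation | Yes, descriptive only |
| Thematic analysis | Open questions | No score comparison |

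For the primary outcomes the same paragraph treats describing and assessing a group difference as two separate steps. Appreciation gets only the first. This is a stated method that does not match the objective, not a detail left to an analysis plan.

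**2. The plan's own figures.** Inputs from Sample size calculation: 50% against 65% uptake, two-sided 5%, 80% power. The usual two-proportion formula with pooled variance and no continuity correction gives:

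n = [1.96 × √(2 × 0.575 × 0.425) + 0.842 × √(0.50 × 0.50 + 0.65 × 0.35)]² / 0.15² = 169.3, rounded up to 170 per group.

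This is the stated figure, and the power at 170 is 80.2%. Then 340 / 4 = 85 probands, and 85 / (0.20 × 0.70 × 0.80) = 758.9, the stated 759. The factor 0.80 is the 20% drop-out, so 85 is what remains after drop-out.

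**3. Precision of the missing contrast.** The documents give no figure for appreciation. With 85 / 2 = 42.5 probands per arm, in SD units:

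95% half-width = 1.96 × √(2 / 42.5) = 1.96 × 0.2169 = 0.43 SD.

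The SD of the 5 to 25 score is not given. Over an assumed range:

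| Assumed SD (points) | 95% half-width (points) |
|---|---|
| 3 | ±1.3 |
| 4 | ±1.7 |
| 5 | ±2.1 |

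If one item were dichotomised, the half-width would be 1.96 × √(2 × 0.25 / 42.5) = 21 percentage points at 50% agreement, and 1.96 × √(2 × 0.16 / 42.5) = 17 points at 80% agreement.

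The difference detectable with 80% power is (1.96 + 0.842) × √(2 / 42.5) = 0.61 SD.

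**4. Relatives.** They complete the questionnaire only if they attend counselling, and attendance is what the intervention is meant to change. Responders in the two arms are therefore not groups formed by randomisation alone, and they are clustered within families. A simple comparison of their scores would not have the protection that the probands' comparison has.

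**The case against.** The best defence is that description was a deliberate choice. The objective is to evaluate appreciation, with no hypothesis or target difference attached. The items are self-constructed, and no psychometric support is reported for summing them, whereas such support is cited for the worry, anxiety and depression, and family communication scales. Modelling the validated scales and describing the satisfaction items is a reasonable division. This argues for modest claims and a choice of simple model. It does not remove the mismatch, because the objective and the strengths list still promise a comparison.

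The article also mentions slight differences between the two arms' questionnaires, and the item list is in a supplement that is not shown. The two intervention-only items may explain this, but it cannot be confirmed that the five proband items are identical in both arms.

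Three stronger readings are tempting, and the documents do not support them:
- **That the trial cannot answer this objective.** The plan does not say frequencies will be pooled over arms. Tables by arm are possible, and a reader could derive an interval from them. What is missing is a pre-stated estimate with its uncertainty.
- **That the plan's 20% drop-out leaves 68 responders and a half-width of 0.48 SD.** The 85 is already net of drop-out, so this counts it twice. The 68 probands mentioned under Trial status are those randomised so far, not expected responders.
- **That appreciation decides whether the approach is acceptable.** No decision rule is tied to it.

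**Conclusion.** The point holds in a limited form. The objective and the strengths list state appreciation as a contrast with usual care, while the analysis section fixes a descriptive method, so no between-arm estimate or interval is planned. If a difference in mean proband score were estimated, its 95% half-width would be about 0.43 SD. This assumes all 85 probands answer, an even split between arms and a normal approximation, with no adjustment for covariates. A gap of that size between two arms shown only as frequencies could be chance.

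This is a secondary outcome and the primary analysis is untouched. It is worth correcting because the remedy is cheap, but it does not threaten the trial's main conclusion.

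**What to change.** In Statistical analysis, replace the sentence on appreciation with text to this effect: the probands' appreciation score (5 to 25) at T1 will be compared between arms as randomised, for example by a linear model with randomisation group and the stratification factors (gender, disease type, hospital), reporting the difference with a 95% confidence interval; item frequencies will be shown by arm in support. First confirm that the five items are the same in both arms.

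Keep the two decisional-conflict items descriptive, since the control arm has no data on them. Keep the relatives' scores descriptive as well, for the selection reason given above. The Objectives section, which now covers "how such a tailored approach is appreciated by both probands and relatives as compared with usual care", should then say that the comparison applies to probands and that relatives' appreciation is described. The strengths list should be aligned with it.

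If description alone was intended throughout, the alternative is to reword the objective and the strengths list as descriptive.

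The cost is one sentence of analysis text and a small edit to the objective, with no new data, visits or participants. The downside is that the interval will be wide and the score is self-constructed, so the result should be reported as an estimate with its uncertainty, not as a test of a pre-specified difference.
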